### Participants

With an estimated attrition rate of 20%, we are recruiting 30 participants between the ages of 18 and 65 with cLBP from the Gainesville, FL community to obtain complete data on 24 participants. We anticipate an additional 75 participants who undergo screening procedures will be ineligible for the study. The sample size was chosen to be large enough to achieve the primary objective (i.e., evaluating feasibility and acceptability) while also considering practical constraints, such as funding and time. Therefore, no power analysis was conducted. Participants will be compensated up to $245 for completing all study procedures. Inclusion and exclusion criteria are displayed in Table 1 and are consistent with definitions for chronic primary low back pain (e.g., back pain associated with emotional distress and/or functional disability and not better accounted for by another condition) [118] and recommendations of the NIH Task Force on Research Standards for cLBP (i.e., participants with cLBP of at least moderate impact that has persisted on more days than not over the past 6 months) [119].

**Table 1 Tab1:** Study inclusion and exclusion criteria

Inclusion criteria	
1. 18–65 years of age	
2. Low back pain that has persisted for at least 3 months and causes pain on most days (more days than not) over the past 6 months.	
3. Average pain intensity ≥ 4 out of 10 for the past week.	
Exclusion criteria	
1. Diagnosis of a systemic rheumatic disease or condition (e.g., rheumatoid arthritis, systemic lupus erythematosus, fibromyalgia).	
2. Asthma, breathing problems, or a respiratory disorder (e.g., chronic obstructive pulmonary disease).	
3. Daily use of opioids.	
4. Uncontrolled hypertension (i.e., systolic blood pressure/diastolic blood pressure > 150/95), orthostatic hypotension (e.g., issues with fainting), or cardiovascular or peripheral arterial disease.	
5. Current or past diagnosis of a neurological disease (e.g., Parkinson’s, multiple sclerosis, epilepsy, vasovagal syncope) or evidence of previous brain injury, including stroke and traumatic brain injury.	
6. Serious psychiatric disorder requiring hospitalization within the past 12 months.	
7. Current substance use disorder or history of hospitalization for treatment of a substance use disorder.	
8. Current participation in another research study involving an intervention or treatment.	
9. Currently pregnant	
10. Any significant comorbidities or issues that, in the opinion of the investigators, could interfere with the study or lead to deleterious effects for the participant.	

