### Recruitment, screening, and enrollment

We will recruit for a “Breathe for Pain Study” widely throughout the Gainesville and University of Florida (UF) community to obtain a sufficient sample of eligible adults with cLBP. Recruitment flyers will be posted throughout the UF Campus (e.g., bulletin boards), as well as at local businesses (e.g., grocery stores), clinical settings (e.g., Clinical Research Center, Orthopedic Institute), and other locations recommended by the UF Clinical and Translational Science Institute Recruitment Center. The recruitment flyer and study information will also be posted online in relevant locations (e.g., The Pain Research and Intervention Center of Excellence Study Listings page). We will also call participants from UF registries, including HealthStreet a community engagement program that connects local residents with relevant research studies.

Potential participants will be screened over the phone using a standardized script. The phone screening involves briefly explaining the purpose of the study, collecting basic demographic and contact information, and determining initial eligibility. Interested and eligible participants will then schedule their first study visit where they will sign the informed consent form in person. Trained study staff will enter responses to the screening questions into a secure REDCap database.

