### Randomization and blinding

The principal investigator ([name]) generated the allocation sequence with a block size of two using an online random number generator (Random.org). Based on the allocation sequence, participants will be randomized (1:1 ratio) using the REDCap Randomization Module at the beginning of Visit 2 to either the Focused- or Standard-BAT. Participants will not be told which intervention they were randomized to until the end of the study, after the 3-month follow-up survey. Due to the inherent difficulties of blinding behavioral interventions, only the participant—not the researcher—will be blind to intervention assignment [102, 114, 120]. Effectiveness of participant blinding will be reported.

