There is currently little research examining the effects of breathing practices in chronic pain populations [23, 24, 170]. Although there is solid theoretical rationale to expect breathing practices and breathwork interventions to be beneficial for individuals suffering with chronic pain [22, 26, 33, 72, 85, 171], high-quality evidence for their efficacy is sparse [23–25]. The relatively few RCTs available reveal that various breathing interventions can improve back pain and pain-related outcomes, but significant heterogeneity in study design, quality, length of follow-ups, and type of breathing interventions limit any strong conclusions [23–25]. Nevertheless, we elected to test this particular conscious connected breathing intervention that also includes breath retention for several reasons. (1) There is empirical evidence supporting that this specific breathing practice influences biological activity relevant to chronic pain, such as decreased inflammation and adaptive immune, nervous, and metabolic activity [47–49, 58]. (2) This breathing technique is relatively easy to learn and quick to practice on one’s own [56]. Therefore, it is advantageous as a remote self-management practice that is expected to be more potent than simply deep breathing and more accessible compared to other emotionally activating breathwork interventions that need to be practiced in a specific setting under the supervision of a trained therapist or facilitator [42–45, 172–175]. (3) Millions of people around the world already engage in this breathing practice on their own^2^, but comparably little scientific research has tested its safety and efficacy. The proposed study is a precursor to a larger efficacy trial which is intended to help bridge this disconnect between widespread public usage and scientific evidence [5, 61]. (4) Finally, because breathing is free and accessible to everyone and the intervention can be practiced remotely with fidelity through the use of replicable audio, video, or app-based media, it has enormous potential for scalability as a self-management strategy.

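### Table 1 does not exclude people who currently or recently practise the tested breathing technique, which weakens participant blinding and the exploratory sham contrast

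*Protocol article*

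**What the plan says.** Eligibility is set in the Participants section of the protocol article: "Inclusion and exclusion criteria are displayed in Table 1". The table has three inclusion and ten exclusion criteria. Criterion 8 is "8. Current participation in another research study involving an intervention or treatment". Criterion 2 concerns asthma and respiratory disorders. Criterion 10 is discretionary: "Any significant comorbidities or issues that, in the opinion of the investigators, could interfere with the study". None names current or past breathwork.

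Three other places bear on this:

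- The Discussion, in giving reasons for choosing this technique, says "Millions of people around the world already engage in this breathing practice on their own".
- Recruitment, screening, and enrollment says "We will recruit for a “Breathe for Pain Study” widely throughout the Gainesville and University of Florida (UF) community".
- Randomization and blinding says "only the participant—not the researcher—will be blind to intervention assignment" and "Participants will not be told which intervention they were randomized to until the end of the study". It adds that the success of participant blinding will be reported.

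Study design explains that neither arm is presented as the active one. The Standard-BAT section describes a control group that gets no instruction in connected breathing, breath holding or mindful body awareness.

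**The concern.** The protocol identifies a large body of existing users, advertises under a title that could attract them, and has no eligibility rule for them. Applied as written, Table 1 admits a current practitioner.

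- **Blinding.** The consent form describes Standard-BAT as deep breathing with relaxation and Focused-BAT as adding instructions that change the breathing pattern. Someone who already knows the technique can match the audio to that description at the first session, in either arm.
- **Contrast.** A practitioner on Standard-BAT can continue the active technique at home between Visit 2 and Visit 3. At-home adherence is judged by time spent on the survey page, which would not show this.
- **Acceptability.** Ratings from people who already use the practice may not represent people learning it.

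What is at stake is the quality of the information that this pilot passes on: how credible the sham is, whether blinding holds, and the responder comparison. The Discussion says that a result favouring control might lead to a modified sham or a three-arm design.

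**Working it through.** **Plan's own figure.** 24 complete participants with 20% attrition: 24 / (1 − 0.20) = 30, which matches the recruitment target. No power analysis was done, so there is no power figure to reproduce. With 1:1 allocation and equal attrition, 24 completers give about 12 per arm.

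**Check of eligibility.** Read one by one against a current practitioner who is otherwise eligible:

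- Criterion 2 does not apply, because it covers disorders.
- Criterion 8 does not apply, because private practice is not a research study.
- Criteria 1, 3 to 7 and 9 concern diagnoses, opioid use, psychiatric or substance-use history and pregnancy.
- Criterion 10 applies only if staff learn of the practice and judge that it interferes.

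So no named criterion excludes this person.

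**Chance of enrolling at least one.** The documents give no rate for the source population, so p is an assumption. For n people the chance is 1 − (1 − p)^n.

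| Assumed p | At least one of 30 enrolled | Expected number in 30 | At least one of 12 controls |
|---|---|---|---|
| 0.5% | 1 − 0.995^30 = 14% | 0.15 | 1 − 0.995^12 = 6% |
| 2% | 1 − 0.98^30 = 45% | 0.6 | 1 − 0.98^12 = 22% |
| 5% | 1 − 0.95^30 = 79% | 1.5 | 1 − 0.95^12 = 46% |
| 10% | 1 − 0.90^30 = 96% | 3.0 | 1 − 0.90^12 = 72% |

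At 0.1% the chance among 30 is 1 − 0.999^30 = 3%.

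**Weight of one person.** In an arm of 12: 1/12 = 8.3 percentage points. Over all 24 completers: 1/24 = 4.2 points. The acceptability criterion is 70% of participants, with no split by arm stated. Over 24 it falls between 16/24 = 66.7% (not met) and 17/24 = 70.8% (met).

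**Dilution of the responder contrast.** Suppose every practitioner on Standard-BAT responded at the Focused-BAT rate. The difference d would then become d × (1 − p). For an assumed d of 25 points: 25 × 0.95 = 23.8 at p = 5%, and 25 × 0.90 = 22.5 at p = 10%. The average dilution is small.

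**Chance imbalance.** With 12 per arm, the probability that the arms differ by two or more practitioners is 14% at p = 5% and 29% at p = 10%.

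**The case against.** The strongest reply is that the pilot's primary outcomes are feasibility and acceptability. The Background disclaims any preliminary efficacy claim, and the Discussion calls the responder comparison exploratory. Criterion 10 could be applied to a practitioner. The telephone script and the supplementary file are not shown, so staff may already ask. Expectations and blinding are both measured, so a breach would be partly visible. Randomisation balances prior practice in expectation. This stands as a reason for modest severity. It does not close the gap: criterion 10 names no such practice, reporting blinding afterwards does not prevent its loss, and balance in expectation cures neither recognition of the arm nor outside practice on sham.

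A reader might infer more than the documents support:

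- **That practice during the 3-month follow-up corrupts the 30% responder result.** It cannot. That target is pre-post and is complete at Visit 3.
- **That practitioners inflate acceptability and adherence.** This is not shown. Someone whose pain persists despite the practice could rate it lower.
- **That earlier benefit distorts the baseline.** Every entrant must still report pain of at least 4 out of 10, and response is measured from the person's own baseline, so this adds little.
- **That an exclusion would secure the blind.** The consent wording lets any participant guess from the content of the recording. Prior practice adds to that weakness but does not create it.
- **That practitioners are bound to appear.** Millions worldwide implies no local rate, and rates well below 2% fit the text equally well.
- **That one person's 8.3 points is bias.** It is the weight of any participant in an arm of 12, and becomes bias only if prior practice changes that person's result.

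**Conclusion.** The gap is real and limited. Table 1 admits current or recent practitioners of the tested technique, while the same article says that there are millions. Such a participant can identify or rule out the active arm, and on sham can continue the active technique during the 5 days. The features exposed are participant blinding and the sham contrast behind an exploratory comparison. Acceptability may also become less representative of newcomers, in a direction that cannot be stated.

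The size rests on an assumed prevalence. From 0.5% to 10%, the chance of at least one such person among 30 runs from about 14% to 96%, and the expected number from 0.15 to 3. Average dilution of the contrast is slight. The practical risk is that one or two people carry noticeable weight in arms of about 12. The documents do not support a conclusion that the primary feasibility result is invalid. The change is worth making because it is cheap and protects what the pilot sets out to test.

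**What to change.** Add one exclusion to Table 1: current or recent regular practice of connected breathing with breath retention (cyclic-hyperventilation breathwork), with the protocol defining recent and regular. Ask about it at telephone screening within a general list of self-management practices, so that the question does not reveal the active arm.

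Excluding anyone with any past training in similar breathwork would be broader than the documents justify. Instead, record other past breathwork or meditation at Visit 1, and any practice outside the assigned sessions at Visit 3. Report both by arm next to the blinding results.

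The cost is one screening item, one eligibility line and two short descriptive items. A few volunteers would be lost, the anticipated 75 ineligible at screening might rise slightly, and the sample would represent people not currently practising the technique. The recruitment target of 30 is unchanged.

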### Recruitment, screening, and enrollment

We will recruit for a “Breathe for Pain Study” widely throughout the Gainesville and University of Florida (UF) community to obtain a sufficient sample of eligible adults with cLBP. Recruitment flyers will be posted throughout the UF Campus (e.g., bulletin boards), as well as at local businesses (e.g., grocery stores), clinical settings (e.g., Clinical Research Center, Orthopedic Institute), and other locations recommended by the UF Clinical and Translational Science Institute Recruitment Center. The recruitment flyer and study information will also be posted online in relevant locations (e.g., The Pain Research and Intervention Center of Excellence Study Listings page). We will also call participants from UF registries, including HealthStreet a community engagement program that connects local residents with relevant research studies.

Potential participants will be screened over the phone using a standardized script. The phone screening involves briefly explaining the purpose of the study, collecting basic demographic and contact information, and determining initial eligibility. Interested and eligible participants will then schedule their first study visit where they will sign the informed consent form in person. Trained study staff will enter responses to the screening questions into a secure REDCap database.

### Randomization and blinding

The principal investigator ([name]) generated the allocation sequence with a block size of two using an online random number generator (Random.org). Based on the allocation sequence, participants will be randomized (1:1 ratio) using the REDCap Randomization Module at the beginning of Visit 2 to either the Focused- or Standard-BAT. Participants will not be told which intervention they were randomized to until the end of the study, after the 3-month follow-up survey. Due to the inherent difficulties of blinding behavioral interventions, only the participant—not the researcher—will be blind to intervention assignment [102, 114, 120]. Effectiveness of participant blinding will be reported.

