### Procedure

Interested participants will complete a telephone screening to determine initial eligibility, and those who qualify will be scheduled for their first visit at the University of Florida Pain Clinical Research Unit to obtain informed consent and complete several baseline assessments and physical functioning tasks. At the end of Visit 1, participants will be scheduled for two additional study visits to occur within a 1-week period (pre-intervention and post-intervention). Participants will also be asked to complete two additional baseline surveys online using REDCap between Visit 1 and Visit 2, which is intended to reduce the participant burden and length of Visit 1. At Visit 2 (pre-intervention), participants will be randomized to the Standard- or Focused-BAT intervention before undergoing quantitative sensory testing procedures. Then, participants will be instructed via an audio-recording to practice their assigned breathing intervention for the first time with the researcher. Physiological data will be collected before, during, and after the breathing practice at both Visit 2 and Visit 3. Following Visit 2, participants will receive an email to practice BAT first thing in the morning if possible by following along to the recording on their own at home. If not possible to practice upon awakening, participants will be asked to practice at least 2 h after a meal. We will attempt to schedule intervention sessions over five consecutive days when possible (Monday–Friday). When not possible, we will require that the last at-home session and last in-person session (BAT sessions 4 and 5) be practiced on consecutive days. At Visit 3, participants will practice their assigned breathing intervention for the 5th and final time and then complete post-intervention questionnaires, quantitative sensory testing procedures, and physical functioning tasks. Finally, participants will be asked to complete 1-, 2-, and 3-month follow-up surveys online using REDCap.

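### Fixed blocks of two with an unblinded researcher make the second allocation of every pair predictable, so concealment fails for about half the sample

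*Protocol article*

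**What the plan says.** All references are to the protocol article.

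- **Sequence (Randomization and blinding).** "The principal investigator" "generated the allocation sequence with a block size of two using an online random number generator". Two is the only block size given, and no strata are mentioned.
- **Release (same section).** "participants will be randomized (1:1 ratio) using the REDCap Randomization Module at the beginning of Visit 2".
- **Blinding (same section).** "only the participant—not the researcher—will be blind to intervention assignment".
- **First session (Procedure).** At Visit 2, after randomisation, "participants will be instructed via an audio-recording to practice their assigned breathing intervention for the first time with the researcher". The Focused-BAT section adds a trial round with the researcher in that arm only. Each allocation is therefore visible to whoever runs the visit.
- **Eligibility (Table 1, exclusion criterion 10).** This criterion covers comorbidities or issues that, "in the opinion of the investigators, could interfere with the study or lead to deleterious effects for the participant".
- **Order of events (Procedure).** Consent and baseline assessment come at Visit 1. Visits 2 and 3 are scheduled at the end of Visit 1, and randomisation follows at Visit 2.
- **Size (Participants).** "we are recruiting 30 participants between the ages of 18 and 65 with cLBP", to obtain complete data on 24.

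**The concern.** Allocation concealment means that those who decide whether and when a person is randomised cannot foresee the arm. With pairs of fixed size, the second member always receives the arm that the first did not. The REDCap module can keep the list from staff, but it cannot hide an allocation that follows logically from one they have just seen.

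For a participant due to fill the second place in a pair, two decisions could be made with the arm known: whether criterion 10 applies, and who is booked into the next Visit 2 slot. Either could shift the mix of participants between arms.

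The result most exposed is the secondary objective, which expects a greater share of CCBR than control participants to reach a 30% pain reduction (Background; Statistical analyses). The Discussion says that a ratio favouring control may lead to a modified sham or a three-arm design, so this comparison can influence the next trial. The Discussion also calls this pilot a smaller-scale version of that trial, so the randomisation scheme may be carried forward with it.

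**Working it through.** **Inputs.** Block size 2, ratio 1:1 and an unblinded researcher (Randomization and blinding); 30 recruited, 24 completers and 20% attrition (Participants). The article gives no figure for predictability.

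**The plan's own figure.** 24 / (1 − 0.20) = 30. This reproduces exactly.

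**Predictability of 1:1 permuted blocks.** All balanced orderings of a block were listed, and two quantities were counted:
- *certain*: allocations fixed by the earlier ones in the same block;
- *correct guesses*: expected hits when always guessing the arm with more places left, with a coin toss at a tie.

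For a block of two, the first place is a coin toss (0.5 expected hits) and the second is certain (1 hit).
- Certain: 1/2 = 50%, or 0.50 × 30 = 15 of 30 (12 if only 24 are randomised).
- Correct guesses: (0.5 + 1)/2 = 75%, or 22.5 of 30.

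| Scheme | Certain | Correct guesses |
|---|---|---|
| Fixed blocks of 2 (as planned) | 50% (15 of 30) | 75% |
| Fixed blocks of 4 | 33.3% (10 of 30) | 70.8% |
| Fixed blocks of 6 | 25% (7.5 of 30) | 68.3% |
| Simple randomisation | 0% | 50% |

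**Varied blocks of 4 and 6, equally likely.** Weighting by block length, (4 × 0.708 + 6 × 0.683)/10 = 0.693, about 69%. Withholding the sizes does not lower this much, because guessing the arm that is behind needs no knowledge of the size. What it removes is most of the certainty.

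**Big-stick rule, imbalance limit 3.** Each allocation is a fair coin toss unless one arm leads by 3, in which case the other arm is forced. Following the imbalance exactly over 30 allocations gives 4.56 expected forced allocations.
- Certain: 4.56/30 = 15%.
- Correct guesses: a forced allocation is a hit and any other is a coin toss, so (4.56 + 0.5 × 25.44)/30 = 17.28/30 = 58%.

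**Sensitivity of the responder comparison.** Assume 24 completers split 12 and 12. One participant is 1/12 = 8.3 percentage points of an arm. If a responder and a non-responder change places between arms, the difference moves by 2/12 = 16.7 points. This shows how little steering would matter numerically. It is not evidence that any occurred.

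**The case against.** Much of the case on the other side stands.

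- **Concealment is not lost altogether.** A reader might infer that allocation is wholly unconcealed. For staff without the list, REDCap can still hide the first member of each pair.
- **Roles are not stated.** A reader might infer that the principal investigator enrols participants, or that visit staff were told the block size. The article says neither, and a condensed article may leave role separation to the full protocol. Strict alternation within pairs is, however, easily inferred from past allocations, and the block size is now published.
- **15 of 30 is an upper bound.** Order is fixed at Visit 2. If several people are between Visits 1 and 2, a given person's place in a pair is not settled when eligibility is judged. Telephone screening also uses a standardised script.
- **Coaching is a separate matter.** A reader might add biased coaching to the harms. The researcher knows the arm at the first session under any scheme, so that follows from unblinding, not block size, and the audio delivery limits it.
- **Feasibility rates are little affected.** Recruitment precedes allocation, and the 70% retention and acceptability thresholds in Statistical analyses are not stated as contrasts between arms.
- **The exposed comparison is exploratory.** The Background disclaims preliminary efficacy claims, and the Discussion cautions against overinterpretation.

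None of this restores concealment for the second member of each pair.

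**Conclusion.** The concern holds in limited form. The second allocation of every pair, up to 15 of 30 (50%), is predictable to anyone who sees the previous allocation and knows or infers the pairing. The overall correct-guess rate is 75%, and a holder of the list could know all 30. This assumes that all 30 are randomised and that the single stated block size was used throughout.

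The consequence is a risk of selection into arms. It falls chiefly on the 30% responder comparison and on the scheme inherited by the efficacy trial. The stronger reading, that the pilot's primary feasibility and acceptability findings are undermined, is not supported, because those are descriptive rates without a stated between-arm contrast. This should be fixed, since the remedy is small, but it does not invalidate the pilot.

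**What to change.** For participants not yet randomised, replace the remaining list by one of the following:

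1. a big-stick rule with an imbalance limit of 3 (about 15% certain and 58% guessable over 30 allocations), which is the stronger option; or
2. randomly varied blocks of 4 and 6, with sizes withheld from visit staff (about 69% guessable, against 75% now).

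An existing team member who does not screen, consent or run visits should generate the list and load it into REDCap, and the protocol should state who can see it. Starting the new list after a completed pair avoids carrying over an imbalance.

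The cost is a new list and a short amendment. Final arm sizes may differ by up to 3, which is tolerable because the article reports no power analysis that depends on exact balance. Some predictability remains under either option.

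The article says the sequence has already been generated and describes recruitment in the present tense, so the number this can still reach is unknown. If enrolment is complete, report the limitation, state who had access to the list, and do not reuse blocks of two in the efficacy trial.
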